### 2.4 Results

#### 2.4.1 Effectiveness outcomes

The primary outcome is a negative LHMBT. It is defined as a rise of hydrogen less than 20 ppm and methane less than 10 ppm within 90 min compared with screening tests.

The secondary outcomes include abdominal symptom relief and alterations in gut microbiota. The key secondary outcome we designed was similar to the relief of IBS global symptoms (Pimentel et al., 2011). Abdominal symptom remission is required to meet at least one of the following criteria: 1) The pain or distension scores of GSRS decrease at least 30% from baseline; 2) Hard stool (1/2 in BSF) and loose stool (6/7 in BSF) reduce more than 50% from baseline.

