**FIGURE 1 F1:**
[figure not shown]
Flow diagram based on the Consolidated Standards of Reporting Trials guidelines (CONSORT): Neg, negative; CRF, case report form.

Before LHMBT, all subjects are supposed to refrain from antibiotic use and discontinue probiotics, laxatives, antidiarrheal and prokinetic agents for 2 weeks. To minimize basal hydrogen excretion, dietary restriction and avoidance of smoking for at least 24 h prior to the test and during the test are recommended. Furthermore, patients are required to avoid coarse grains, milk, juice, and alcohol in the evening before the test. Fasting for 8–12 h before the procedure is needed. Before the examination, subjects use 20 mL antiseptic mouthwash (0.05% chlorhexidine) to eliminate fermentation by oral bacteria. End-expiratory breath samples will be collected just before the ingestion of 10 g (15 mL) of lactulose in a 250 mL water solution. Gas samples are collected every 15 min until 90 min and tested immediately by the methane-hydrogen breathing analyzer DA6000 (Sunvou Medical Electronics Co., Ltd., Wuxi, China). A rise in hydrogen of ≥20 part per million (ppm) by 90 min with elevated or normal methane was considered positive. Patients with only methane levels ≥10 ppm are not eligible (Rezaie et al., 2017).

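### The primary-endpoint sentence names only the screening test as comparator, so it allows scoring rules that give opposite results for an unchanged positive breath test

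*Protocol article*

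**What the plan says.** Section 2.4.1 (Effectiveness outcomes) states "The primary outcome is a negative LHMBT" and defines it as "a rise of hydrogen less than 20 ppm and methane less than 10 ppm within 90 min compared with screening tests". It does not mention the sample taken before lactulose on the day of the follow-up test.

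Section 2.3.1 (Screening, text below Figure 1) describes a single test. The first sample is the fasting one: "End-expiratory breath samples will be collected just before the ingestion of 10 g (15 mL) of lactulose". Sampling then follows: "Gas samples are collected every 15 min until 90 min and tested immediately". Positivity for entry is set as "A rise in hydrogen of ≥20 part per million (ppm) by 90 min with elevated or normal methane was considered positive", with no reference to any other test. Methane appears there as an absolute value: "Patients with only methane levels ≥10 ppm are not eligible". The consensus criterion cited in the Introduction has the same form, a hydrogen rise or a methane level during one test.

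The abstract gives non-inferiority of berberine to rifaximin as the primary hypothesis. Section 2.6 plans on eradication rates of 72.9% (rifaximin) and 69.8% (berberine), one-sided α = 0.025, 80% power and 82 patients per arm. Section 2.1 describes the trial as open-label.

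**The concern.** Every enrolled patient had a positive hydrogen test at screening. If the follow-up test is judged by how far it has risen above that screening test, persistent overgrowth can look like clearance, because the reference is itself a positive test. Failures would then be scored as successes in both arms, both rates would move up, and any real deficit of berberine would shrink. In a non-inferiority trial that error favours the conclusion sought.

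A second problem remains even if the error is never made. A primary-endpoint sentence that can be scored in more than one way leaves a choice open, and in an open-label trial that choice could be settled after allocation is known.

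**Working it through.** **1. The two rules side by side.**

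| | Section 2.3.1 (entry) | Section 2.4.1 (outcome) |
|---|---|---|
| Hydrogen | rise of at least 20 ppm by 90 min within one test | rise below 20 ppm within 90 min, relative to screening |
| Reference named | none outside the test; a pre-lactulose sample is taken | the screening test only |
| Methane | level, cut-off 10 ppm | below 10 ppm; level or change not stated |

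The outcome sentence carries two reference points. The 90-minute window belongs to one test, while the closing phrase points to another test weeks earlier.

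**2. One unchanged patient under each reading.** Assumed for illustration: fasting hydrogen 5 ppm and peak 45 ppm at both visits.

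| Reference for hydrogen | Calculation | Result (cut-off 20 ppm) |
|---|---|---|
| Same-day pre-lactulose sample | 45 − 5 = 40 | positive |
| Screening peak or matching time point | 45 − 45 = 0 | negative |
| Screening rise | (45 − 5) − (45 − 5) = 0 | negative |
| Screening fasting value | 45 − 5 = 40 | positive |

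The last row agrees with the same-day rule only because fasting hydrogen did not move. In general, rise against screening fasting = same-day rise + (follow-up fasting − screening fasting). A shift in fasting hydrogen between visits is therefore added to the result and can carry it across 20 ppm in either direction.

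**3. Effect on the treatment difference if failures are misclassified.** Let p be the true negative rate and f the share of true failures scored negative, assumed equal in both arms. The scored rate is p + f(1 − p), so the scored difference is (1 − f) × the true difference. With the planned rates the true difference is 72.9 − 69.8 = 3.1 points.

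| f (assumed) | Rifaximin | Berberine | Difference (points) |
|---|---|---|---|
| 0 | 72.9% | 69.8% | 3.1 |
| 0.25 | 79.7% | 77.3% | 2.3 |
| 0.5 | 86.5% | 84.9% | 1.6 |
| 0.75 | 93.2% | 92.4% | 0.8 |
| 1 | 100% | 100% | 0 |

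**4. Effect on the error rate, as an illustration.** Section 2.6 states no margin, so its 82 per arm cannot be reproduced directly. The margin it implies is (0.729 − 0.698) + (1.960 + 0.842) × √[(0.729 × 0.271 + 0.698 × 0.302)/82] = 0.031 + 0.198 = 0.229.

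Suppose berberine were truly worse by exactly that amount (72.9% v 50.0%). With a and b the scored rifaximin and berberine rates, the chance of declaring non-inferiority is Φ{[0.229 − (a − b)]/√[(a(1 − a) + b(1 − b))/82] − 1.960}:

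| f (assumed) | a | b | Difference | Chance of declaring non-inferiority |
|---|---|---|---|---|
| 0 | 0.729 | 0.500 | 0.229 | 2.5% |
| 0.25 | 0.797 | 0.625 | 0.172 | 12.8% |
| 0.5 | 0.865 | 0.750 | 0.114 | 46.7% |
| 0.75 | 0.932 | 0.875 | 0.057 | 96.2% |

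These figures apply only if one of the readings that clears an unchanged patient is used, and f itself is not known.

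**The case against.** The best defence is that an ordinary within-test rule was meant. The outcome is named as a test result rather than a change score. The 90-minute window has little meaning for a comparison between visits. The hydrogen and methane cut-offs are the complement of the consensus positive test cited in the Introduction. The planned eradication rates of about 70% also fit a conventional negative test better than a rule that pushes rates toward 100%. On this view the closing phrase is a loose contrast with the positive screening result. All of that is fair, and it makes the within-test rise the more likely intention.

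It also rules out a stronger reading that a reader might infer: that the trial does score change from screening and so counts patients with unchanged overgrowth as cured. The documents do not support this. They do not show how tests are being read, and even a screening comparator leaves the unchanged patient positive if the reference is the screening fasting value.

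The same restraint applies to methane. A reader might infer that a high but stable methane value would pass. That requires carrying the word for a rise over from hydrogen to methane. The Introduction and Section 2.3.1 treat methane as a level, and that is the natural reading here too.

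The article condenses a fuller protocol that may be clearer, but this point concerns a rule that the article does state. Likely intent does not remove the comparator from the sentence, and no other comparator is named there.

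**Conclusion.** The primary-endpoint sentence is wrong as written. It names a comparator that does not match the within-test rule in Section 2.3.1, and it permits scoring rules that give opposite results for the same unchanged patient. Some of those rules bias the trial toward non-inferiority. The screening-fasting rule instead lets drift in fasting hydrogen affect the result.

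The size depends on which rule is applied and cannot be fixed from the documents. The only general statement is the factor (1 − f), which assumes equal misclassification in both arms; for example, misclassifying half of failures halves the true difference. The error rates in the working also rest on a margin inferred from the sample size, because none is stated. Nothing shows that any test has been misread. The correction is warranted because this is the primary outcome of an open-label non-inferiority trial.

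**What to change.** Reconcile Section 2.4.1 with the Introduction and Section 2.3.1. Delete the reference to the screening test and define a negative test wholly within the follow-up test: hydrogen rises by less than 20 ppm above that test's own pre-lactulose sample at every sampling time up to 90 min, and methane levels are below 10 ppm up to 90 min.

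Confirm, and record, that tests already read were scored by this rule. Re-score from the recorded ppm values only if they were not.

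The cost is a one-sentence amendment and a check of the scoring procedure. No new measurements are needed, and the sample size does not change on this account.

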#### 2.4.2 Assessment of harms

The study investigator will exclude those with any physical problems that may limit participation with berberine or rifaximin exposures. Participants will be asked to report any adverse events (AEs) experienced during the study period. Participants with adverse events (e.g., dizziness, headache, loss of taste, dull sensation, diplopia, vertigo, palpitations, hot flashes, dyspnea, hematochezia, rash, back pain, muscle spasm, muscle weakness, hematuria, fever, flu-like symptoms after intervention) will be advised to consult their physician to provide healthcare as appropriate. The investigator will record the details of the frequency and severity of adverse events.

### 2.5 Randomization and allocation

Participants will be randomized after baseline assessment to either berberine or rifaximin intervention with a 1:1 allocation. A laboratory staff member, not the investigator, used Statistical Package for Social Science Version 26.0 software (SPSS V.26.0) to produce 180 random numbers after setting the starting point according to the simple randomization. The patient codes were divided into two groups (A for berberine and B for rifaximin) according to the size of the number to form a random allocation table. The corresponding information of each code was assembled into the envelope seal. Thus, the principal investigator will remain blinded to the randomization process. Participants will be aware of the group to which they are allocated.

### 2.6 Sample size

We calculated the sample size based on the primary outcome of eradication rate. Gatta and Scarpignato (2017) published a meta-analysis in which the overall eradication rate of rifaximin for SIBO patients according to per-protocol analysis was 72.9%. Therefore, the null hypothesis is postulated to be a rate of 72.9% (*P*
_
*0*
_). We proposed that the effective rate of berberine is 69.8% (*P*
_
*1*
_) (Wang et al., 2002; Chen et al., 2015). Using the non-inferiority design with unilateral *α* = 0.025 and power 1-β = 0.8, 82 participants will be enrolled in each group. However, assuming a 10% attrition rate, we will aim to recruit 90 participants per group.

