Berberine is a natural pentacyclic isoquinoline alkaloid extracted from many popular medicine plants such as the genus *Berberis*, *Coptis* and *Hydrastis* (Wang et al., 2017). There is already evidence that the structural and numerical changes in the gut microbiota under pathological conditions can be reversed by berberine (Jia et al., 2019), which mediates modulatory effects on microglial activation and visceral hypersensitivity (Zhang et al., 2021), and ameliorates intestinal inflammation in humans through antibacterial action (Gong et al., 2017; Habtemariam, 2020). Berberine enhanced the composition of beneficial bacteria such as *Bacteroides*, *Bifidobacterium*, *Lactobacillus*, and *Akkermansia* (Fang et al., 2021). Furthermore, it could alleviate colon inflammation by regulating interferon-gamma and interleukin-17A-producing lamina propria CD4 (+) T cells (Takahara et al., 2019). It has been proven to significantly decrease diarrhea and abdominal pain scores in diarrhea-predominant IBS patients (Chen et al., 2015). Berberine effects to the gut may provide therapeutic targets for SIBO. Chedid et al. (2014) confirmed that herbal therapy containing berberine is equivalent to rifaximin for the resolution of SIBO. However, there is little evidence investigating the potential effect of berberine as a single agent in SIBO patients. In the present study, we aimed to evaluate the effects of berberine and rifaximin on patients with SIBO (BRIEF-SIBO study). The effectiveness outcomes included a negative lactulose hydrogen methane breath test (LHMBT) and clinical symptom remission. Different gut microbiome spectra in SIBO patients treated with berberine and rifaximin may provide a potential explanation.

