### 2.9 Statistical analysis

Patients who finish at least one postmedication evaluation after randomization and subsequent treatment constitute the study full analysis set (FAS) as well as the primary group of efficacy assessment, according to the intention to treatment (ITT) principle. Patients who meet the criteria and complete the observation before medication without other affected treatments during the trial will be included in the study per protocol set (PPS) as the secondary group of efficacy assessment. The study safety set consists of all cases who have safety evaluation data after taking at least one kind of drug. Rubin’s method of multiple imputation will be performed for missing values to restore natural variability and uncertainty. The complete and imputed datasets will be combined and analyzed (Little et al., 2012). Complete case analysis is used for fecal microbiota on the nature of the outcome.

Analysis will be conducted using SPSS V.26.0. The quantitative and qualitative variables were reported as mean ± standard deviation (SD), median ± interquartile range (IQR), and number (frequency). Univariate analysis of variance (ANOVA) will examine differences between groups for variables with continuous data. χ2 tests will examine differences between groups for categorical variables. Unadjusted ANOVA and adjusted analysis of covariance models will compare differences in scores from baseline and postintervention data within and between groups using FAS and PPS. Variable correlations will be analyzed through Spearman’s correlation analysis. Statistical significance was defined as a *p*-value less than 0.05.

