## 3 Discussion

The pharmacology of berberine has been extensively explored and revealed multifunctional activities, including anti-inflammatory (Wang et al., 2017), anticancer (Chen et al., 2019; Sun et al., 2019; Gong et al., 2020), antidiabetic (Gong et al., 2017), antihyperlipidemic and cardioprotective effects, based on its regulation of gut microbiota. To the best of our knowledge, the BRIEF-SIBO study is the first clinical trial assessing the eradication effects of a two-week intervention with berberine in SIBO patients. The effect of berberine will be fully verified by using rifaximin as the positive control. The findings of this study may have implications for the management of SIBO, especially increasing the awareness of both clinicians and patients who suffer from long-term abdominal discomfort and avoiding excessive examination. We also expect to promote clinical diagnosis and efficient management. Intervention patterns will refine and inform the development of future berberine medication designed for patients with SIBO.

The goal of therapy in SIBO is not only to eradicate the small intestinal microbiota but also to improve symptoms (Quigley et al., 2020). Thus, we set abdominal symptom remission as an important point of effectiveness. The secondary outcomes also include other symptom improvements from GSRS and alterations in the gut microbiome. Different microbiome spectra in SIBO patients after treatment with berberine and rifaximin may provide a potential explanation. Predictors may be considered in clinical practice to target SIBO patients most likely to benefit from the varied intervention.

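### The 80% power in section 2.6 rests on a per-protocol rifaximin rate and a berberine rate whose basis as an eradication rate is not shown, so it is not shown to be the power of the primary FAS analysis

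*Protocol article*

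**What the plan says.** Section 2.6 names the endpoint used for sizing: "We calculated the sample size based on the primary outcome of eradication rate". For the control arm it relies on a meta-analysis in which "the overall eradication rate of rifaximin for SIBO patients according to per-protocol analysis was 72.9" per cent. For the experimental arm it states: "We proposed that the effective rate of berberine is 69.8" per cent, citing two sources. With one-sided alpha 0.025 and 80% power it arrives at 82 per group, and recruits 90 per group to allow for 10% attrition. No non-inferiority margin appears in the article.

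Section 2.9 says that randomised and treated patients with at least one evaluation after medication "constitute the study full analysis set (FAS) as well as the primary group of efficacy assessment". The PPS is secondary, and missing values are multiply imputed.

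On the evidence for berberine, section 1 describes one of the two cited sources only as showing that the drug can "significantly decrease diarrhea and abdominal pain scores in diarrhea-predominant IBS patients". The other source is not described anywhere. Section 1 adds that "there is little evidence investigating the potential effect of berberine as a single agent in SIBO patients", and section 3 says that, to the authors' knowledge, "the BRIEF-SIBO study is the first clinical trial assessing the eradication effects of a two-week intervention with berberine in SIBO patients".

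**The concern.** A power figure belongs to one analysis: one endpoint, one set of patients, one margin. Here the control rate comes from patients who completed treatment as planned, while the primary analysis also keeps patients who did not. The only allowance made is for attrition, and that changes the number of patients and not the rates.

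The berberine figure is called an effective rate. The one described source concerns symptoms in a different condition, and the authors say that there is little single-agent evidence in SIBO. The article does not show how 69.8% was obtained as a rate of negative breath tests. Yet the expected deficit of 3.1 points (72.9 − 69.8), to which non-inferiority power is very sensitive, depends on it.

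At stake is the reading of a negative result. If non-inferiority is not shown, a reader needs to know whether the trial had 80% power for the analysis that failed or only for a more favourable one.

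**Working it through.** **Inputs.** From section 2.6: rifaximin pC = 0.729, berberine pT = 0.698, one-sided alpha 0.025 (z = 1.960), power 0.80 (z = 0.842), 82 per group analysed, 90 per group recruited. The margin M is not given.

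**Step 1: the margin that 82 per group implies.** With n = (1.960 + 0.842)² × V / (M − (pC − pT))² and V = pC(1 − pC) + pT(1 − pT):

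- V = 0.1976 + 0.2108 = 0.4084
- M = 0.031 + √(7.849 × 0.4084 / 82) = 0.031 + 0.1977 = 0.2287

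So 82 per group reproduces with a margin of about 22.9 points. With the same rates, a 20-point margin would need 113 per group and a 15-point margin 227. A 20-point margin comes close to the stated size (81) only if the expected 3.1-point deficit is left out. The 22.9 points are therefore inferred, not stated.

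**Step 2: power at other rates.** Power = Φ((M − (pC − pT)) / √(V/n) − 1.960), with M = 0.2287. I show 90 per arm, if everyone recruited is analysed, and 82, if attrition leaves the planned number. All rates other than 72.9/69.8 are assumptions, because the article gives no FAS rates.

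| Rifaximin / berberine (%) | 82 per arm | 90 per arm |
|---|---|---|
| 72.9 / 69.8 (as planned) | 80.0% (by construction) | 83.5% |
| 70 / 67 | 78.2% | 81.9% |
| 65.6 / 62.8 (both × 0.9) | 76.5% | 80.2% |
| 60 / 57 | 73.4% | 77.2% |
| 72.9 / 68 | 71.4% | 75.4% |
| 72.9 / 65 | 54.7% | 58.6% |

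The last digit can move by 0.1 with the rounding of the margin. Worked example, 72.9/65 with 82 per arm: V = 0.1976 + 0.2275 = 0.4251; √(0.4251/82) = 0.0720; (0.2287 − 0.079)/0.0720 = 2.079; Φ(2.079 − 1.960) = Φ(0.119) = 54.7%.

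**Step 3: separating the two inputs.** Rows two to four lower both rates and keep the gap near 3 points; this is the per-protocol versus FAS question. Power moves because the variance grows, and only slowly. Rows five and six hold rifaximin and lower berberine; the gap becomes 4.9 and 7.9 points and power falls quickly.

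**Step 4: dependence on the margin.** At a 20-point margin the planned rates themselves would give 66.8% with 82 per arm and 70.8% with 90. Without a stated margin, no power figure for this trial can be confirmed.

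**The case against.** Four arguments on the other side have force.

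- **The FAS mismatch costs little.** The FAS needs only one evaluation after medication, and missing values are imputed, not counted as failures. If dropouts were counted as failures they would stay in the denominator, so the diluted rates belong with about 90 per arm, where power is 80.2%. Section 2.8 also replaces patients who withdraw. This stands: the first part of the point is modest.
- **The second source for 69.8% is not described.** A reader might infer that 69.8% is a symptom response rate and that the 3.1-point deficit compares unlike quantities. The article does not support that. It describes one source of two, and section 2.6 sets both rates on the scale of eradication. What can be said is that the basis is not shown. Section 1 also reports that a herbal therapy containing berberine was equivalent to rifaximin in resolving SIBO, which gives some support for similar rates, though not for berberine alone.
- **The rate is already worded as a proposal.** True, and scarce evidence explains why a rate had to be assumed. It does not show that the rate is wrong, but it is a reason to show power over a range.
- **Any non-inferiority design loses power as the true deficit grows.** Also true. The figures at 68% and 65% show sensitivity to the least supported input; they do not show a planning mistake.

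What remains is that nothing in the article links either input to an expected eradication rate in the FAS.

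**Conclusion.** The point holds in a limited form. Section 2.6 states 80% power on a per-protocol control rate and on a berberine rate whose basis as a breath-test eradication rate is not shown, while section 2.9 tests in the FAS. The 80% is therefore not shown to be the power of the primary analysis.

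The per-protocol basis alone takes power to about 77-80% with 90 per arm or 73-77% with 82, for assumed rates between 65.6/62.8 and 60/57. The berberine rate is the more sensitive input: about 71-75% power if it is 68%, and 55-59% if it is 65%. All of this rests on assumed rates and on a margin back-solved from 82 per group.

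A reader might go further and call the trial underpowered, or the calculation wrong. Neither follows. The stated size reproduces at a margin near 22.9 points, and the true FAS rates are unknown. This is a weakness in the planning basis, worth correcting because the correction is cheap.

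**What to change.** **Section 2.6.** Say explicitly that 72.9% is a per-protocol rate while the primary analysis is in the FAS. Say that 69.8% is an assumption about breath-test eradication and how it was derived. State the margin used. Replace the single 80% with the FAS power of the 180 planned patients over a range of assumed eradication rates in each arm, as in the table above.

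**Section 2.9.** Conclude non-inferiority only if the FAS and PPS analyses both meet the margin. Section 2.7 allows patients with limited symptom response to be offered other interventions, including a change of medication. The FAS keeps such patients, which can pull the arms together and favour a finding of non-inferiority. Both sets are already defined.

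**Cost.** Some wording and a small table; no added patients. The stated power becomes less favourable, and requiring both sets somewhat lowers the chance of success. That joint requirement should be reflected when power is restated.

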## Abstract

**Introduction:** Small intestinal bacterial overgrowth (SIBO) leads to non-specific abdominal discomfort and nutrient malabsorption. Currently, rifaximin is widely applied in SIBO based on its antibacterial and non-absorbable nature. Berberine is a natural component of many popular medicine plants that ameliorates intestinal inflammation in humans through its modification of the gut microbiota. Potential effect of berberine to the gut may provide therapeutic target for SIBO. We aimed to evaluate the effect of berberine compared with rifaximin on SIBO patients.

**Methods:** This is an investigator-initiated, single-center, open-label, double-arm randomized controlled trial, termed BRIEF-SIBO (Berberine and rifaximin effects for small intestinal bacterial overgrowth). In total, 180 patients will be recruited and allocated to an intervention group (berberine) and a control group (rifaximin). Each participant will receive one 400 mg drug twice a day (800 mg daily) for 2 weeks. The total follow-up period is 6 weeks from the start of medication. The primary outcome is a negative breath test. The secondary outcomes include abdominal symptom relief and alteration in gut microbiota. Efficacy assessment will be performed every 2 weeks, as well as safety assessment during the treatment. The primary hypothesis is that berberine is not inferior to rifaximin for SIBO.

**Discussion:** The BRIEF-SIBO study is the first clinical trial assessing the eradication effects of 2 weeks of berberine treatment in SIBO patients. The effect of berberine will be fully verified by using rifaximin as the positive control. The findings of this study may have implications for the management of SIBO, especially increasing the awareness of both physicians and patients who are suffering from long-term abdominal discomfort and avoiding excessive examination.

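### The non-inferiority sample size in section 2.6 states no margin; on its own inputs, 82 per arm gives 80% power only at a margin of about 23 points or wider

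*Protocol article*

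**What the plan says.** The Abstract sets the aim: "The primary hypothesis is that berberine is not inferior to rifaximin for SIBO". Section 2.6 (Sample size) then lists its inputs:

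- Control rate, from a published meta-analysis: "the overall eradication rate of rifaximin for SIBO patients according to per-protocol analysis was 72.9" per cent.
- Null: "Therefore, the null hypothesis is postulated to be a rate of 72.9" per cent.
- Test rate: "We proposed that the effective rate of berberine is 69.8" per cent.
- One-sided alpha and power: "0.025 and power 1-β = 0.8".
- Result: "82 participants will be enrolled in each group".
- Inflation to 90 per group, "assuming a 10% attrition rate".

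Section 2.5 randomises "with a 1:1 allocation". Section 2.9 (Statistical analysis) makes the full analysis set (FAS) the primary efficacy set and the per-protocol set secondary. For categorical variables it plans chi-square tests of between-group differences, with significance at p below 0.05. The Abstract and sections 2.6 and 2.9 contain no non-inferiority margin.

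**The concern.** A non-inferiority sample size cannot be computed without a margin, and section 2.6 reports every input except that one. In its place stands a null that fixes a single rate. A non-inferiority null concerns the difference between arms: that berberine is worse than rifaximin by the margin or more. Section 2.9 does not fill the gap, because a chi-square test of no difference does not test that null and a non-significant result would not establish non-inferiority.

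Two things are at stake. The margin decides whether the primary hypothesis is met, and the article does not let a reader see what it is. The 80% power also cannot be checked, and the margin it implies is wide enough that readers should be told of it.

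**Working it through.** **Inputs (sections 2.5 and 2.6).** pC = 0.729, pT = 0.698, deficit 0.729 − 0.698 = 0.031, one-sided alpha 0.025 (z = 1.960), power 0.80 (z = 0.842), 1:1 allocation.

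**Formula (unpooled variance, margin M on the difference scale).**

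n per arm = (1.960 + 0.842)² × [pC(1 − pC) + pT(1 − pT)] / (M − 0.031)²

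The bracket is 0.729 × 0.271 + 0.698 × 0.302 = 0.19756 + 0.21080 = 0.40836. With (z sum)² = 7.849 the numerator is 3.205.

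**Reproducing 82.** This is not possible directly, because M is missing. Solving for it:

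M = 0.031 + √(3.205/82) = 0.031 + 0.1977 = 0.2287, or 22.9 points.

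Other methods give 22.9 points (pooled variance), 22.5 (control-arm variance), about 22.7 (Farrington-Manning) and about 24 (continuity correction). If all 90 per arm were evaluable, M = 0.031 + √(3.205/90) = 0.2197, about 22 points. A superiority formula gives 3338 per arm, so it does not explain 82.

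**Other margins at the stated rates.** Power = Φ[(M − 0.031)/√(0.40836/n) − 1.960]. The documents give none of the margins in this table; they are illustrations.

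| Margin | n per arm for 80% | Power, n = 82 | Power, n = 90 |
|---|---|---|---|
| 10 points | 674 | 16% | 17% |
| 15 points | 227 | 39% | 42% |
| 20 points | 113 | 67% | 71% |
| 23 points | 81 | 81% | 84% |

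Farrington-Manning power with 82 per arm is 16%, 40% and 67% at 10, 15 and 20 points.

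**Could 82 come from 20 points?** Only if the true difference is set to zero:

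- both rates 0.729: 7.849 × 0.39512/0.04 = 77.5, so 78
- variance from the two stated rates: 3.205/0.04 = 80.1, so 81
- both rates 0.698: 7.849 × 0.42159/0.04 = 82.7, so 83

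This range contains 82, but a zero difference contradicts the stated 69.8%. Margins of 10 and 15 points need 311 and 138 per arm even with zero difference at the rifaximin rate.

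**What 22.9 points means.** The null boundary is 0.729 − 0.229 = 0.500. With 82 per arm the 95% half-width at the stated rates is 1.960 × √(0.40836/82) = 0.138. The observed difference must therefore be no worse than about −0.229 + 0.138 = −0.09.

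**Attrition.** 90 × 0.9 = 81 evaluable; 82/0.9 = 91.1, so 92. The shortfall is trivial and nothing here rests on it.

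**Control rate (assumed values).** Keeping the 3.1-point deficit, a 22.9-point margin and 82 per arm, the power is:

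- 72.9% vs 69.8%: 80%
- 65% vs 61.9%: bracket 0.22750 + 0.23584 = 0.46334; Φ(0.1977/0.0752 − 1.960) = 75%
- 60% vs 56.9%: bracket 0.24000 + 0.24524 = 0.48524; Φ(0.1977/0.0769 − 1.960) = 73%

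**The case against.** The strongest reply is that this is a condensed article. A figure of 82 could hardly have been produced without some margin, so one was probably set, and it may stand in the full protocol or an analysis plan not shown. With an input missing, no arithmetic error can be proved. The wording of the null may be only a loose way of labelling the control rate.

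Much of this stands, and it limits what can be claimed. Several stronger readings are tempting but unsupported:

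- *That the stated 80% power is false.* It is correct if the margin is about 23 points or wider. The 10-, 15- and 20-point margins are not the sponsor's.
- *That berberine clearing 50% against 72.9% would be declared not inferior.* That is the boundary of the null at 22.9 points, where the chance of success is about 2.5%, the stated alpha. Observed rates of 72.9% and 50% would give a lower limit near −37 points, a clear failure.
- *That the margin will be chosen after the data.* The article does not show this. It shows only that a reader cannot confirm the margin was set in advance, in an open-label trial still recruiting at submission.
- *That the FAS rate is materially lower than 72.9%.* The article gives no FAS rate. Its FAS requires a post-medication evaluation, and missing values are multiply imputed rather than counted as failures.

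Condensation does not dispose of the point. Section 2.6 prints the other inputs and the result, puts a single-rate null where the margin belongs, and section 2.9 names a test that does not address non-inferiority.

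**Conclusion.** The point holds as an unstated margin together with a misstated null. On the article's own rates, alpha and power, 82 per arm requires a margin of about 23 points or wider (22.5 to 24 by method; about 22 if all 90 per arm are evaluable). There are two natural explanations. One is an undisclosed margin of that size, which could not exclude a true berberine rate just above 50% against 72.9%. The other is a 20-point margin computed without the 3.1-point deficit. That would contradict the stated 69.8% and leave about 67% power with 82 per arm, or 71% with 90. The documents do not show which applies. Either way section 2.6 needs correcting, because the primary hypothesis has no stated threshold and no matching test. The results assume a margin on the risk-difference scale and the normal approximation. The mismatch between a per-protocol control rate and a FAS primary analysis is a secondary note, and its effect on power depends on assumed rates.

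**What to change.** In section 2.6:

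1. Replace the single-rate null with H0: p(berberine) − p(rifaximin) ≤ −margin.
2. State the margin actually used, with its justification, and fix it before outcomes are compared by arm.
3. Restate the power that about 81 to 82 evaluable (90 randomised) per arm gives at that margin with 72.9% and 69.8%. As a secondary step, show it over an assumed range of lower FAS rates.
4. If the margin is about 23 points, say so and limit the conclusion to excluding a loss of that size.

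In section 2.9, judge the primary outcome by the lower limit of the two-sided 95% confidence interval for the difference against −margin, which matches the one-sided 0.025 level.

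The cost is rewording and one recalculation. No extra patients are needed, but the stated power may become less favourable.
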